#### Blinding and unblinding

2.7.3

While the control group is non-active, outcome assessors and data analysts remain strictly blinded to group assignments. Unblinding is only permissible in the event of a medical emergency in which the group assignment is critical to the participant’s safety.

#### Data management and missing data

2.7.4

Data entry is performed by trained personnel with range checks to promote quality. Missing data will be handled using multiple imputation or the Last Observation Carried Forward method. Sensitivity analyses will be conducted to assess the robustness of the primary findings with respect to participant adherence levels.

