Following completion of the initial six-month intervention phase, participants will be given the option to voluntarily continue recitation practice. The selection of a six-month intervention period is informed by the MEMO+ (Méthode d’Entrainement pour Mémoire Optimale) protocol developed by Sylvie Belleville and colleagues (Bier et al., 2015). Later studies from the same research team have demonstrated that participants receiving structured cognitive training exhibited significant improvements in memory recall performance, with effects persisting for at least 6 months post-intervention (Belleville et al., 2018). Furthermore, long-term follow-up over 5 years revealed that individuals who had undergone cognitive training experienced a slower decline in delayed memory performance and Montreal Cognitive Assessment (MoCA) scores compared with control groups (Belleville et al., 2024). These findings underscore the sustained benefits and potential long-term impact of continuous cognitive training.

Additional support for the selected intervention duration is derived from studies examining other forms of cognitively engaging activities. For example, interventions involving structured calligraphy practice have demonstrated that extending training duration over a six-month period leads to significant alterations in functional brain connectivity (Lee et al., 2024). Specifically, increased connectivity has been observed between the medial prefrontal cortex (mPFC) and right lateral temporal cortex (LTC), mPFC and right inferior parietal lobe (IPL), left hippocampal formation (HF) and right LTC, as well as between the left HF and right IPL (Lee et al., 2024). These findings suggest that prolonged engagement (6 months) in cognitively demanding tasks may induce measurable neuro-modulatory effects at the network level.

Taken together, a 6-month intervention period represents a balanced design choice: it is sufficiently long to allow for detectable behavioral and neurobiological changes, yet not so prolonged as to compromise participant adherence. Accordingly, outcome assessments will be conducted at baseline (time of recruitment), immediately after the six-month intervention, and at one-year and two-year follow-ups, with annual assessments thereafter until participants are no longer able to complete evaluations. The study will be conducted at China Medical University Hospital, primarily within the outpatient clinics of the Departments of Neurology or Psychiatry.

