### Sample size

2.3

Our sample size calculation is based on selecting functional MRI changes as an exploratory mechanistic outcome measure, given their higher sensitivity than neuropsychological tests at the preclinical stage in SCD patients (Viviano and Damoiseaux, 2020). This approach differs from many previous cognitive intervention studies that have used neuropsychological test scores as primary outcomes. The target sample size is informed by prior neuroimaging studies in individuals with SCD, where changes in functional MRI parameters served as the primary outcomes (Bhome et al., 2018), while also considering feasibility constraints (Belleville et al., 2023). Accordingly, we plan to recruit 60 participants, with 30 individuals allocated to each group. To account for an anticipated attrition rate of approximately 20%, based on dropout rates reported in comparable longitudinal cognitive intervention studies in older adults (Cheng et al., 2024; Fernandez-Gamez et al., 2026), we will initially enroll 72 participants (36 per group), with the expectation that at least 60 will complete the study.

If neuropsychological test scores were used as the primary outcome, a substantially larger sample size would be required. An *a priori* power analysis was conducted using G*Power version 3.1.9.4 (Heinrich Heine University, Düsseldorf, Germany), based on a two-group comparison of continuous outcomes within the t-test family (“Means: Difference between two independent means”). Equal group allocation was assumed (N₂/N₁ = 1), and a one-tailed test was selected given the directional hypothesis that the intervention would improve outcomes. The anticipated standardized effect size was set at Cohen’s d = 0.18, derived from prior meta-analytic evidence indicating a small-to-moderate effect consistent with neuroimaging-based outcomes in SCD populations (Bhome et al., 2018). With a Type I error rate (*α*) of 0.05 and statistical power (1 − *β*) of 0.80, the estimated required sample size would be 383 participants per group (total *N* = 766; df = 764; actual power = 0.8006). Given the extensive multimodal assessments and longitudinal design of the present study, recruiting a sample of this magnitude is not feasible. Therefore, this study is designed as an exploratory, hypothesis-generating trial with a smaller sample size, aiming to provide preliminary effect estimates and inform future large-scale confirmatory studies.

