##### Statistical analysis

2.5.2.5

Statistical analyses will be conducted within the framework of the general linear model (GLM). For the primary clinical outcomes (e.g., subjective cognitive measures, neuropsychological test scores), a linear mixed-effects model will be used to handle the repeated-measures structure of the data throughout baseline, post-intervention, and follow-ups, with time, group, and group × time interaction as fixed effects, and subject as a random effect. This approach naturally accommodates missing data under the missing-at-random (MAR) assumption without requiring complete cases. The primary analysis will follow the intention-to-treat principle, including all randomized participants regardless of adherence or dropout, with missing values handled using multiple imputation based on baseline characteristics and available follow-up data. A per-protocol sensitivity analysis will also be conducted, restricted to participants who complete at least 80% of the intervention sessions. Covariates to be included in adjusted models will comprise age, sex, years of education, and baseline cognitive scores, selected *a priori* for their known associations with cognitive outcomes in SCD populations.

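### Section 2.7.4 permits last observation carried forward with no limit on its use, which is inconsistent with the missing-at-random analysis in section 2.5.2.5 and can distort the pilot's effect sizes

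*Protocol article*

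**What the plan says.** Two sections of the protocol article set the missing-data approach.

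- **Section 2.5.2.5 (Statistical analysis)** covers the clinical outcomes: "For the primary clinical outcomes (e.g., subjective cognitive measures, neuropsychological test scores), a linear mixed-effects model will be used". Of this model it says "This approach naturally accommodates missing data under the missing-at-random (MAR) assumption without requiring complete cases". The same paragraph makes the primary analysis intention-to-treat in all randomised participants, "with missing values handled using multiple imputation based on baseline characteristics and available follow-up data".
- **Section 2.7.4 (Data management and missing data)** says "Missing data will be handled using multiple imputation or the Last Observation Carried Forward method". It names no outcome or visit and does not confine LOCF to a sensitivity analysis. The only sensitivity analysis it mentions concerns adherence: "Sensitivity analyses will be conducted to assess the robustness of the primary findings with respect to participant adherence levels".

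Three other statements bear on the consequences. Section 2.3 anticipates attrition of about 20% and says "we will initially enroll 72 participants (36 per group), with the expectation that at least 60 will complete the study". Section 2.1 schedules assessments at baseline, 6 months, one year and two years, "with annual assessments thereafter until participants are no longer able to complete evaluations". Sections 2.1 and 2.3 give preliminary effect sizes for later trials as a main purpose of the study.

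**The concern.** An analyst could follow section 2.7.4 to the letter, use LOCF, and produce an analysis that section 2.5.2.5 does not describe. LOCF replaces every missing value with the participant's last observed one, which amounts to assuming no change after dropout. A MAR model instead predicts the missing value from the observed course of similar participants.

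This matters in two places. For a baseline-to-6-month outcome the last observation is baseline, so every dropout is given a change of exactly zero. At the annual clinical visits, some people will be missing because they can no longer be assessed, and LOCF gives them an earlier and possibly better score. In both cases the filled-in values are then analysed as if observed.

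The estimates are meant to be used to size later trials, so a distortion here carries forward into those designs.

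**Working it through.** **1. The two sections compared.** The mixed model and multiple imputation both rest on MAR and can be used together. Section 2.5.2.5 is unclear about which applies where, but it does not contradict itself. LOCF rests on a different assumption, and the word "or" in section 2.7.4 comes with no criterion. The inconsistency is therefore LOCF against section 2.5.2.5.

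**2. The plan's own figure.** Section 2.3 gives 383 per group for d = 0.18, one-sided alpha 0.05, power 0.80. The exact t-test solution is 382.3, so 383, with power 0.8006. The figure reproduces. It does not depend on the missing-data rule, but it gives a scale for what follows.

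**3. Baseline to 6 months.** Let p be the share missing at 6 months, at random and equal in both arms. Section 2.3 gives about 20% attrition for the study as a whole; placing all of it by 6 months is an assumption.

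- Mean difference kept = 1 − p. For p = 10%, 20%, 30% this is 0.90, 0.80, 0.70.
- At p = 20% with the SD unchanged: 0.18 × 0.80 = 0.144.
- The zeros also shrink the SD of change, by √(1 − p) = √0.80 = 0.894 when mean change is small. Standardised by that SD: 0.144 / 0.894 = 0.161.
- Put back into the section 2.3 calculation, d = 0.144 needs 597 per group and d = 0.161 needs 478, against 383.
- The standard error of change is 0.894 of its full-data value and 0.80 of the completers' value.

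**4. Later annual visits.** Suppose there is no true effect and those who leave would have declined by δ SD after their last visit. LOCF then creates a difference of δ × (p₁ − p₂) in favour of the arm with more dropout. The documents give neither dropout by arm nor δ, so all inputs are assumed.

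| Dropout | δ = 0.1 SD | δ = 0.3 SD | δ = 0.5 SD |
|---|---|---|---|
| 20% vs 20% | 0 | 0 | 0 |
| 25% vs 10% | 0.015 | 0.045 | 0.075 |
| 30% vs 10% | 0.020 | 0.060 | 0.100 |

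**5. Simulation.** Inputs: 36 per arm (section 2.3) and visits at 0, 0.5, 1 and 2 years (section 2.1). Assumed: SD 1, between-visit correlation 0.7, control decline 0.3 SD per year, nominal two-year dropout as shown, completely at random or MAR, 4,000 runs per scenario. LOCF with baseline-adjusted comparison at two years was set against a MAR regression estimate.

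| True effect at 2 years | Dropout, control / intervention | LOCF | MAR estimate |
|---|---|---|---|
| 0 | 20 / 20% | 0.00 | 0.00 to −0.01 |
| 0 | 10 / 30% | +0.06 to +0.10 | 0.00 |
| 0 | 30 / 10% | −0.06 to −0.09 | 0.00 |
| 0.40 | 20 / 20% | 0.33 to 0.34 | 0.40 |
| 0.40 | 10 / 30% | 0.36 to 0.40 | 0.40 |
| 0.40 | 30 / 10% | 0.28 to 0.30 | 0.40 |

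With no effect and unequal dropout, LOCF rejected in 6.4% to 8.6% of runs at a nominal two-sided 5%. Its model standard error was 0.163 to 0.170, against a sampling SD of 0.187 to 0.201 for the MAR estimate. Scenario by scenario it was about 10% smaller (1 − 0.170/0.189) to 19% smaller (1 − 0.163/0.201).

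**The case against.** The strongest reply is that section 2.5.2.5 already assigns multiple imputation to the intention-to-treat primary analysis, and that section 2.7.4 is one general sentence under trial administration. Sections 2.1 and 2.7.3 also keep data analysts blinded, section 2.1 until the primary analysis is complete. This limits the point. A reader might infer that the primary method is simply open, or that it will be picked once results are known; the documents do not support that. What stands is that section 2.7.4 permits LOCF without scope and nothing elsewhere withdraws it. The annual visits also continue well past the 6-month assessment, after which blinding of the analysts may have ended.

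A reader might also infer three conflicting rules. There are not three: the mixed model and multiple imputation share one assumption.

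Nor does LOCF always bias the effect and its standard error. With no effect and equal dropout the bias is nil, and in one simulated scenario (true effect 0.40, 10/30% dropout completely at random) opposing biases cancelled. The LOCF standard error matches the spread of the LOCF estimate itself; it is too small only by comparison with a MAR-valid analysis. At 6 months, effect and standard error both fall to 0.80 of their completer values, so the test statistic is about that of a completer analysis.

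Finally, the decline argument does not reach the outcome that section 3.3 calls primary, a 6-month imaging change expected to increase. It applies to the later clinical visits, and the introduction describes some subjective decline as stable or reversible. The value d = 0.18 comes from a calculation that section 2.3 sets aside as not feasible, so it serves here only as a scale. The 0.045 SD figure is small beside the standard error of a standardised difference with 30 per arm, √(2/30) = 0.26.

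**Conclusion.** The point holds in limited form. Section 2.7.4 allows LOCF for any outcome and visit with no rule for choosing it, and this does not fit section 2.5.2.5. If the option is used, a 6-month mean difference keeps 80% of its true size when 20% are missing at random in both arms by then. On the section 2.3 effect size, d becomes 0.144 or about 0.161, depending on which SD is used. At later clinical visits the size and direction depend on decline and on dropout by arm, neither of which the documents give; over the assumed grid the spurious difference runs from 0 to 0.10 SD. The standard error is about 10% to 19% below that of a MAR-valid analysis in the simulated scenarios.

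These are not large amounts in a study declared hypothesis-generating. They matter because effect sizes are what the pilot is meant to deliver, and because the error is avoidable. It should be corrected.

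**What to change.** Delete LOCF from section 2.7.4 and make that section agree with section 2.5.2.5. State one rule by type of outcome:

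- for repeated clinical outcomes, the mixed model on all observed data from all randomised participants, under MAR, as the primary analysis;
- multiple imputation where a single-time-point model or missing covariates require it.

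Optionally, add a sensitivity analysis for departures from MAR at the later annual visits, where inability to complete the assessment may itself reflect decline. This goes beyond correcting the inconsistency and could be left to the statistical analysis plan.

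The cost is a change of wording and, if the option is taken, a little extra analysis. No participants, visits or measurements are added.

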## Discussion

3

### Theoretical framework and mechanistic rationale

3.1

Among non-pharmacological cognitive interventions for SCD, computerized cognitive training (CCT) — the most extensively studied approach — yields a small but statistically significant overall effect on untrained cognitive outcomes in healthy older adults (Hedges’ *g* = 0.18, 95% CI 0.14 to 0.23), with benefits primarily in processing speed, working memory, and non-verbal memory, though with considerable heterogeneity across trials (*I*^2^ = 58%) and wide prediction intervals spanning negligible to moderate effects (−0.36 to 0.73) (Lampit et al., 2020). Exercise-based interventions represent a second major modality; a network meta-analysis of exercise interventions specifically in SCD populations found that, while exercise improved multiple cognitive domains, it remained unclear which type of exercise was most effective, and no single modality demonstrated consistent superiority (Chen et al., 2024). Combined cognitive-physical interventions produce a small advantage over single-domain cognitive training on executive functions, but achieve similar effects on memory and global cognition (Rieker et al., 2022). Notably, a network meta-analysis of pharmacological and non-pharmacological interventions for SCD across 56 randomized controlled trials found that education-based programs ranked highest for improving both memory and global cognition — above CCT, physical exercise, and pharmacological approaches — suggesting that structured, content-rich verbal-cognitive engagement may be a particularly promising avenue (Roheger et al., 2021).

Despite growing evidence for the general benefit of cognitive interventions in aging, the magnitude and consistency of effects vary substantially across trials, limiting the conclusions that can be drawn from aggregate findings. A comprehensive systematic review of interventions specifically targeting SCD found that, while cognitive training yielded a small statistically significant improvement in objective performance overall (*g* = 0.13, 95% CI 0.01 to 0.25), effect sizes became non-significant when studies used active control groups (*g* = 0.02) or reported global cognitive outcomes (*g* = 0.06), indicating that published effects may largely reflect expectancy and practice artifacts rather than genuine cognitive benefit (Roheger et al., 2021). Heterogeneity of effects is attributable to multiple sources, including variability in SCD diagnostic criteria, differences in intervention dosage and delivery format, inconsistent outcome measurement across domains, and the absence of standardized follow-up periods. In addition, the methodological quality of published cognitive intervention trials in SCD and related preclinical populations remains a significant concern. The majority of trials suffer from one or more of the following limitations: inadequate sample sizes, short intervention durations with no long-term follow-up, outcomes measured only on trained tasks rather than ecologically valid measures, high or unclear risk of bias due to lack of assessor blinding, and failure to conduct intention-to-treat analyses (Roheger et al., 2021). Beyond sample size and reporting concerns, cognitive intervention trials face several systematic biases that may inflate apparent treatment effects. The most pervasive is performance bias from expectancy effects, in which participants believe they are receiving an active intervention and therefore may perform better on outcome assessments regardless of the intervention’s true efficacy. A systematic review of computerized cognitive training trials in healthy older adults found that only 47% included an active control condition, and only 21% measured participants’ expectations — meaning that the majority of published positive findings cannot rule out expectancy as a major contributor to the observed effects (Masurovsky, 2020). To address the gap limited by short follow-up periods, inadequate control of participant expectancy effects, and a predominant reliance on behavioral outcomes without accompanying biological measures in previous studies, this pilot study will incorporate long-term annual follow-ups, administer the credibility and expectancy questionnaire to monitor and statistically adjust for expectancy at baseline and post-intervention, and employ a multimodal assessment framework integrating cognitive, neuroimaging, metabolomic, and gut microbiota measures.

Epidemiological evidence has consistently identified modifiable lifestyle factors associated with reduced risk of cognitive decline and dementia. A landmark study published in *The Lancet Neurology* demonstrated that rich social networks, engagement in mental activities, and regular physical activity represent three major protective factors against cognitive decline, Alzheimer’s disease, and dementia in older adults. Among these, mental activities were particularly associated with preserved verbal intelligence and reduced rates of cognitive deterioration. Proposed mechanisms include the cognitive reserve hypothesis, the vascular hypothesis, and the stress hypothesis (Fratiglioni et al., 2004).

The cognitive reserve framework posits that lifelong intellectual enrichment enhances neural efficiency, capacity, and flexibility, thereby allowing individuals to better tolerate age-related neuropathology before clinical symptoms emerge. Substantial interindividual variability exists in cognitive aging trajectories; for example, some individuals in their eighties may demonstrate superior cognitive performance compared to middle-aged adults (Cabeza et al., 2018). A 20-year longitudinal study involving 3,777 older adults concluded that education was a key determinant of this variability, with higher educational attainment associated with delayed clinical manifestation of cognitive impairment by approximately 7 years (Amieva et al., 2014). These findings support the concepts of cognitive maintenance and reserve, suggesting that education and sustained mental engagement enhance neuroplasticity and increase resilience to neuropathological burden. Importantly, cognitive reserve is not static. It accumulates through education and occupational complexity during midlife but may decline in later life depending on physical health, psychosocial stress, and ongoing cognitive engagement (Cabeza et al., 2018). Structured cognitive training may therefore serve as a modifiable intervention to reinforce reserve mechanisms during aging. In the present study, fMRI will be employed to detect subtle alterations in neural activation patterns and network connectivity associated with recitation-based cognitive training.

Education does not only contribute to cognitive reserve but also modulates neural recruitment patterns during cognitive tasks. A study led by Sylvie Belleville demonstrated that individuals with higher educational attainment exhibited distinct activation patterns following cognitive training using the method of loci. Participants engaged in memory training for 1 h per day over three consecutive weeks. During memory retrieval tasks, individuals with higher education levels showed differential activation in the right middle and inferior temporal gyri (Brodmann areas 20, 21, and 37), regions associated with semantic processing and memory integration (Belleville et al., 2023). These findings suggest that education influences compensatory neural strategies and training-induced plasticity. Accordingly, years of education will be recorded in our cohort, and the CRI-q (Lin et al., 2025) will be administered to quantify reserve-related variables. Where sample size permits, subgroup analyses stratified by educational attainment will be conducted to examine differential intervention effects.

Beyond cognitive reserve mechanisms, the stress hypothesis provides an additional neurobiological framework. This model emphasizes dysregulation of the HPA axis. Chronic stress or maladaptive stress responses may lead to sustained glucocorticoid hypersecretion, downregulation of hippocampal glucocorticoid receptors, and impairment of the negative feedback loop regulating cortisol levels. Prolonged exposure to elevated glucocorticoids is associated with hippocampal neuronal loss and has been implicated in the pathogenesis of dementia (Fratiglioni et al., 2004). Through comprehensive biomarker profiling of blood samples, including metabolic and inflammatory markers, our study aims to explore whether structured memorization training may modulate systemic pathways related to stress regulation and neuroprotection.

Conceptually, Chinese Classics recitation departs from the dominant single-domain training paradigm underlying conventional cognitive training. Programs such as computerized working memory or attention training isolate one cognitive process and train it through repetitive, decontextualized trials, an approach associated with reliable near-transfer but inconsistent far-transfer (Owen et al., 2010; Simons et al., 2016). Recitation, by contrast, requires the concurrent integration of sustained attention, verbal learning, episodic memory retrieval, semantic comprehension, and executive control during continuous oral production — a structure more consistent with enrichment-type interventions linked to cognitive reserve, in which simultaneous multi-system engagement is hypothesized to support broader, distributed benefit rather than process-specific gains (Stern, 2009). This conceptual distinction extends to stimulus content and learning mechanisms. Where conventional tasks use abstract, content-free stimuli optimized for psychometric precision, recitation uses semantically dense, culturally meaningful text; under levels-of-processing accounts of memory, such meaningful material is expected to support deeper and more durable encoding than decontextualized information (Craik and Lockhart, 1972). The intervention also incorporates repeated oral retrieval of previously learned passages, engaging retrieval practice (testing effect) mechanisms associated with enhanced long-term retention (Roediger and Karpicke, 2006) — a feature largely absent from trial-based computerized training, which typically emphasizes recognition or reaction-based responding rather than self-generated recall.

Practically, the two approaches also differ in delivery. Conventional cognitive training is typically administered as discrete, algorithmically adaptive trials on an individual basis, with difficulty calibrated by software in response to real-time performance. Recitation is self-paced and continuous, often delivered in a group or instructor-guided setting, with dosage and repetition flexibly determined by the participant’s progress rather than by automated adjustment. This difference in implementation, combined with the use of culturally familiar material, gives recitation greater ecological validity, as it more closely resembles real-world language and memory processes than computerized drills and may support more sustained engagement. In addition to these conceptual and practical distinctions, the two approaches are also hypothesized to differ physiologically. Within the stress-axis framework, the rhythmic vocalization and breath regulation inherent in recitation are hypothesized to engage vagal and HPA-axis pathways, offering a candidate physiological mechanism — distinct from standard training paradigms — through which behavioral intervention could influence stress-related neuroplasticity and gut-brain signaling.

Collectively, the following theoretical models: cognitive reserve, neural compensation, and stress-axis modulation, provide the mechanistic foundation for the present trial. While multiple potential mechanisms may underlie the effects of classical recitation on cognitive function, our primary hypothesis is that classical recitation training will be associated with greater change in resting-state functional connectivity within the hippocampal-default mode network than controls, consistent with intervention-induced neuroplasticity in memory-relevant circuits. Our secondary hypothesis proposes that the stress-axis modulation pathway, whereby recitation-induced enhancement of vagal tone and attenuation of HPA axis reactivity diminish stress-related gut dysbiosis, consequently fostering the production of beneficial microbial metabolites and neuroplasticity. Exploratory hypotheses include associations between classical recitation and shifts in gut microbiota composition and in circulating metabolomic profiles. By integrating behavioral training with multimodal biological measurements, including neuroimaging and peripheral biomarker analyses, this study seeks to bridge cognitive neuroscience theory with measurable physiological outcomes in individuals with subjective cognitive decline.

